### Diagnostic criteria

3.2

#### Traditional Chinese medicine diagnostic criteria

3.2.1

Taking diagnosis and standard for evaluating curative effect formulated by the state administration of traditional Chinese medicine acute encephalopathy team as reference.

##### Diagnostic criteria for stroke

3.2.1.1

Primary symptom: hemiplegia, unconsciousness, sluggish speech, hemianesthesia, and deviation of the eye and mouth.Secondary symptoms: headache, vertigo, changes in pupil and spirit, choking when drinking water, strabismus, and ataxia.Acute onset with inducement and often premonitory signs.Most of the patients are over 40 years old.Patients matching more than 2 primary symptoms or 1 primary symptom along with 2 secondary symptoms can be diagnosed in combination with the onset, inducement, premonitory signs, and age; the diagnosis can also be made with imaging examination.

##### Staging criterion

3.2.1.2

The acute stage: within 2 weeks after stroke attacking viscera, no more than 1 month after stroke attacking meridians.The convalescent stage: 2 weeks to 6 months after the onset.The sequela stage: 6 months after onset.

#### Western medicine diagnostic criteria

3.2.2

##### Diagnostic criteria for cerebral infarction

3.2.2.1

Taking guidelines for diagnosis and treatment of acute ischemic stroke in China in 2010 as reference.

3.2.2.1.1 Diagnostic criteria

Acute onset;The focal neurological deficit, limited numbers of comprehensive neurological deficit;Signs and symptoms lasting more than 24 hours;Exclusion of non-vascular encephalopathy;Images of brain CT or MRI show ischemic duty focus and exclusion of cerebral hemorrhage and other diseases.

3.2.2.1.2 Classificatory diagnosis

There are kinds of clinical pathology types due to the difference in the location and size of cerebral infarction, collateral compensative capacity, secondary cerebral edema, and so on. As their treatment is very different, rapid and accurate classificatory is required in the acute stage, especially in the ultra-early stage (within 3–6 hours).

3.2.2.1.2.1 Clinical classification

Oxfordshire community stroke project (OCSP) classification: patients can be classified rapidly according to clinical manifestations instead of imaging results, which is ahead of conventional CT and MRI and indicates the size and location of occluded vessels and infarcted lesions. This method is easy for the clinical application and has important significance in guiding treatment and evaluating prognosis.

OCSP clinical classification criteria

Total anterior circulation infarction (TACI): it is shown as triad syndrome, that is, complete middle cerebral artery (MCA) syndrome, including dysfunction of higher neurological activity in the brain (consciousness disorder, aphasia, miscalculation, spatial orientation disorder, and so on), homonymous hemianopia, the more serious motor and/or sensory disorders in the opposite 3 parts (face, upper limb, and lower limb). Most of the cerebral infarction is caused by the occlusion of proximal MCA and a few are internal carotid artery siphon.

Partial anterior circulation infarcts (PACI): it is shown as 2 of the above triad syndrome, or only dysfunction of high-level neurological activity in the brain, or sensorimotor deficit limited than TACI, which indicates that it is caused by the middle or minor occlusion of distal MCA and branches or ACA and branches.

Posterior circulation infarcts (POCI): it is shown as various degrees of the vertebrobasilar syndrome, including ipsilateral cerebral nerve paralysis and contralateral sensorimotor dysfunction, bilateral sensorimotor dysfunction, binocular coordination, and cerebellar dysfunction without long bundle syndrome or visual field defect. Different size of the brainstem and cerebellar infarction is caused by the occlusion of vertebral–basilar arterial and branches.

Lacunar infarction (LACI): it is shown as the lacunar syndrome, such as pure motor hemiplegia, pure sensory stroke, ataxia hemiplegia, and dysarthric-clumsy hand syndrome. Most of the small lacunar infarcts are caused by lesions of basal ganglia or small perforating branches of pontine.

Posterior circulation infarction (POCI): various vertebrobasilar syndrome: ipsilateral cerebral palsy and contralateral sensorimotor dysfunction; bilateral sensorimotor dysfunction; binocular cooperative activity and cerebellar dysfunction; no long bundle syndrome or visual field defect. It is caused by occlusion of the vertebrobasilar artery and branches. Lacunar infarction (lacI): lacunar syndrome, such as pure motor hemiplegia, pure sensory stroke, ataxia hemiplegia, hand clumsiness dysarthria syndrome, etc. Most of them are small lacunar lesions caused by the small perforating branches of basal ganglia or pons.

3.2.2.1.2.2 Structural imaging (CT) classification

Large infarction: more than 1 lobe with a maximum cross-sectional diameter of more than 5 cm.Middle infarct: less than 1 lobe with a maximum cross-sectional diameter of 3.1 to 5 cm.Small infarction: maximum cross-sectional diameter of 1.6 to 3 cm.Lacunar infarction: maximum cross-sectional diameter of less than 1.5 cm.

##### Diagnostic criteria for intracerebral hemorrhage (ICH)

3.2.2.2

Taking the diagnostic criteria of ICH in guidelines for diagnosis and treatment of ICH as reference.

Combined with CT and other imaging examinations, ICH is easy to be diagnosed based on the clinical signs and symptoms, such as sudden onset, severe headache, vomiting, and neurological dysfunction. However, there is no gold standard for the diagnosis of primary cerebral hemorrhage, especially hypertensive cerebral hemorrhage. So it is necessary to exclude all kinds of secondary cerebral hemorrhage to avoid misdiagnosis. Making the final diagnosis need to meet all the following criteria:

A definite history of hypertension;Typical bleeding sites (including basal ganglia, ventricles, thalamus, brainstem, and cerebellar hemisphere);Excluding secondary cerebral vessels disease with DSA/CTA/MRA;Excluding diseases like the brain tumor or cavernous malformations (CM) with enhanced MRI examination in the early stage (within 72 hours) or the late stage (3 weeks after the disappearance of hematoma);Excluding various coagulopathy.

### Inclusion criteria

3.3

Age 30 to 75 years;Meet the diagnostic criteria for cerebral infarction and intracerebral hemorrhage;Meet the diagnostic criteria for stroke and staging criterion in traditional Chinese medicine,The onset time of cerebral infarction or intracerebral hemorrhage is within 3 months; the evaluation of modified Barthel index is less than 70 points, and the evaluation of modified Rankin scale is more than 3 points;Modified Barthel index < 70, MRS ≥ 3;Patients and his family members both voluntarily agree to participate in this clinical trial and sign the informed consent.

### Exclusion criteria

3.4

(1)Lacking definitive imaging examination, such as CT or MRI.(2)Special types of stroke: individuals with progressive stroke or intracerebral hemorrhage after cerebral infarction or with disturbance of consciousness.(3)Individuals with mild syndrome; individuals with slight stroke or slight neurological defect and the evaluation of modified Barthel index is more than 70 points; individuals without disability or with rapid improvement of symptoms, such as individuals with the transient ischemic attack (TIA) and (RIND).(4)Individuals who receive treatment of dredging blocking vessels in the acute stage (such as thrombolysis, arterial thrombectomy, super early thrombus aspiration, and stenting).(5)Individuals with bleeding tendency; individuals with serious bleeding within 3 months.(6)Individuals with severe cardiac insufficiency, atrial fibrillation, heart valve disease, or individuals after heart valve replacement.(7)Individuals with other diseases, which can influence the function of limb movement; individuals with limb motor dysfunction caused by claudication, rheumatoid arthritis, or gouty arthritis before treatment.(8)Similar diseases: individuals with CT or MRI imaging of neurological symptoms caused by non-vascular factors; individuals who have suffered from intracranial neurobiology or arteriovenous malformation, aneurysm or neuro-tumor, or individuals with cranial neuro-tumor visible in imaging; individuals with cerebral trauma, multiple sclerosis, cerebral parasites, seizures, hysterical paralysis, or cerebral amyloid angiopathy.(9)Individuals may be exposed to risks or damage by participating in this study from recruitment investigators’ points of view.(10)Disabled individuals (blind, deaf, dumb, mental disorders, mental disorders, and any other limb disability which can affect the evaluation of neurological impairment).(11)Individuals who have known or suspected of having a history of drug or alcohol abuse, or considered inappropriate by the recruitment investigators.(12)Allergic individuals: people who have known or suspected of being allergic to related substances in this study.(13)Individuals who are in other clinical trials or have participated in other drug trials in the past 3 months.

### Informed consent (ethical considerations)

3.5

This trial is designed in accordance with the principles of the Declaration of Helsinkiand and relevant Chinese clinical trial research criteria and regulations. The trial cannot be implemented until the research project and the ethics committee of each research units consider, agree, and sign the approval opinions. During the clinical trial, any modification of the protocol should be approved by the ethics committee. Prior to enrollment, clinical research physicians should fully introduce the objective, process, and possible risks of the study to each patient or his designated agent, along with a written informed consent. The trial cannot be carried out until the patient or his agents or family members signs the informed consent.

### Collection and preservation of the baseline data

3.6

We have established the clinical research regulation, standardized operating procedure, data collection, and analysis of the multi-center randomized blind controlled trial. We will collect and evaluate 360 cases of patients with cerebral infarction or intercerebral hemorrhage no more than 3 months and the treatment will last 4 weeks.

## Intervention

4

Participants are divided into 2 groups, the control group (routine treatment group) and the experimental group (eye-acupuncture and routine treatment group).

### Normalized operation of eye-acupuncture combined with rehabilitation training therapy

4.1

The rehabilitation programs are determined according to the patient's condition and the evaluation of rehabilitation. Based on the principle for the selection of acupoints, patients receive eye-acupuncture treatment and keep the needles retained in the process of rehabilitation. The rehabilitation training is carried out by physical therapists and the program includes eye-acupuncture physical therapy, eye-acupuncture occupational therapy, eye-acupuncture speech training, eye-acupuncture cognitive rehabilitation training, eye-acupuncture cognitive rehabilitation training, and eye-acupuncture pain rehabilitation techniques. The needles are withdrawn in 5 minutes after the rehabilitation. Researchers should rotate the needle with the thumb and forefinger lightly and slowly until half of the needle is pulled out. Then withdraw the needle slowly and press the hole with a dry cotton ball after pulling out the needle immediately. Pick up the needle and hold the handle with the thumb and food fingers of the needle-holding hand. After gently turning, slowly pull out the needle 1/2, and then slowly pull out the needle (shown in Fig. 2).

1.*Eye-acupuncture physical therapy*: Eye-acupuncture physical therapy includes eye-acupuncture exercise therapy and eye-acupuncture equipment training. Needles are embedded in the liver region, kidney region, upper-jiao region, and lower-jiao region on both sides. The rehabilitation programs are determined by functional evaluation. Participants are expected to recover or improve dysfunction by taking various kinds of exercise training with hands or equipment, which include limb intelligent feedback training system, gait analysis treadmill, intelligent sports training device, electric erecting bed training, dysphagia therapeutic apparatus, scene interactive rehabilitation system, balance function examination training system, and so on.2.*Eye-acupuncture occupational therapy*: Needles are embedded in the liver region, kidney region, upper-jiao region, and lower-jiao region on both sides of the eyes. At the same time, participants get training and treatment by choosing purposeful activities based on their needs in daily life, family life, social intercourse, and career.3.*Eye-acupuncture speech training*: Needles are embedded in the upper-jiao region, lower-jiao region, heart region, and spleen region on both sides of the eyes for participants with speech disorder. At the same time, conducting the conventional speech training4.*Eye-acupuncture cognitive rehabilitation training*: Needles are embedded in the upper-jiao region, lower-jiao region, heart region, and kidney region on both sides of the eyes. At the same time, rehabilitation treatment for attention, memory, calculation, thinking, the ability to solve problems and execute, and perceptual disorder is implemented in order to improve cognitive function and activity of daily living.5.*Eye-acupuncture pain rehabilitation techniques*: Needles are embedded in the upper-jiao region, lower-jiao region, heart region, and spleen region on both sides of the eyes. At the same time, participants get rehabilitation training based on their major dysfunction.6.*Needles selection*: Specialized needles for eye-acupuncture combined with rehabilitation training therapy at the length of 0.30 mm × 8 mm, 0.25 mm × 8 mm, 0.30 mm × 7 mm, 0.25 mm × 7 mm (Patent Number: CN201320166807).7.*Position selection*: in the supine position.

**Figure 2 F2:**
[figure not shown]
Diagram of acupoint location of eye-acupuncture.

### Normalized operation and acupoint selection in body acupuncture

4.2

Upper limbs: Jianyu (LI15), Quchi (LI11), Shousanli (LI10), Waiguan (TE5), Hegu (LI4), Yangchi (TE4), Zhongzhu (TE3).

Lower limbs: Huantiao (GB30), Weizhong (BL40), Weiyang (BL39), Yanglingquan (GB34), Zusanli (ST36), Sanyinjiao (SP6), Jiexi (ST41), Kunlun (BL60).

(Taking the recovery stage of stroke in the fifth edition of acupuncture and moxibustion, a textbook for TCM planning in colleges and universities, as reference.)

### Therapeutic schedule

4.3

Participants are randomly divided into 2 groups and receive different treatments after enrollment.

Basic treatment in 2 groups: taking standardized treatment and the relevant contents in Chinese guidelines for the prevention and treatment of cerebrovascular diseases 2010 and Chinese guidelines for the diagnosis and treatment of cerebral hemorrhage 2014.

The control group: carrying out routine rehabilitation training (for example, physical therapy, occupational therapy, cognitive training, speech training, and swallowing training) on the basis of basic treatment. If participants need body acupuncture treatment, referring to the normalized operation and acupoint selection in body acupuncture above-mentioned.

The experimental group: carrying out eye-acupuncture combined with rehabilitation training (for example, physical therapy, occupational therapy, cognitive training, speech training, and swallowing training). The time of training with needles in the eyes should be less than 6 hours. Needles need to be withdrawn after training. If participants need body acupuncture treatment, referring to the normalized operation and acupoint selection in body acupuncture above-mentioned.

### The course of the treatment

4.4

All participants will receive treatment once a day for 5 consecutive days and rest for 2 days a week. The treatment will last for 4 weeks in total.

## Effect measurement

5

### Therapeutic outcomes

5.1

#### Primary therapeutic outcomes

5.1.1

ADL scales (modified Barthel index);Simple Fugl–Meyer motor function score;Functional magnetic resonance imaging (fMRI) of the brain in the resting state.

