### Study design

2.1

A multi-center, block randomized, parallel control trial has been designed to assess the effect of eye-acupuncture combined with rehabilitation training therapy on limb dysfunction in patients with stroke in the convalescent stage. 360 patients will be enrolled. In order to verify and evaluate the clinical effects, outcomes will be measured by the activity of daily living (ADL) scales (modified Barthel index), modified Rankin scales (MRS), TCM syndrome score, simple Fugl–Meyer motor function score, water swallow test, western aphasia battery (WAB), Montreal cognitive assessment (MoCA) and 2 brain function remodeling indexes, growth-associated protein-43 (GAP-43), and microtubule-associated protein-2 (MAP-2) in the infarction border zone. It is expected to develop the technical standards of eye-acupuncture combined with rehabilitation training therapy, to form the characteristic TCM rehabilitation technology and diagnosis and treatment of stroke in the convalescent stage, to optimize the outcome assessment and to form the characteristic TCM rehabilitation evaluation method and hierarchical medical treatment system.

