### Grouping

2.3

According to previous studies, the effective rate of the routine treatment group is 80 percent and the morbidity rate of eye-acupuncture and routine treatment group is 90 percent. Suppose *α* is 0.05 (one side) and *β* is 0.20. Calculated by PASS 11, the sample size in both groups is 157. With an estimated 10 percent dropout rate, the sample size is 175. Thus 360 patients will be recruited and divided into 2 groups in the study, with half of them (n = 180) in the control group (routine treatment group) and others (n = 180) in the experimental group (eye-acupuncture combined with routine treatment group).

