### Randomization

2.5

Stratified block randomization will be used in the study based on the SAS proc plan sentence at the appropriate length. The seed is set as the running time of the program and the case number of the experimental group and the control group is in a ratio of 1:1. The serial number 001-360 which corresponds to a participant will be assigned to each center randomly. Centers are ordered in the alphabetical list by the initial letter of pinyin and offer treatment in increasing sequence.

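### Three unranked primary outcomes rest on one sample size for a single unidentified response rate, so the stated 5% error and 80% power are not secured for the trial's claim

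*Protocol article*

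**What the plan says.** - **Primary outcomes (5.1.1, and the same three in the abstract):** "ADL scales (modified Barthel index);Simple Fugl–Meyer motor function score;Functional magnetic resonance imaging (fMRI) of the brain in the resting state". No order or hierarchy is given.
- **Sample size (2.3):** for the control arm, "the effective rate of the routine treatment group is 80 percent"; for the experimental arm, "the morbidity rate of eye-acupuncture and routine treatment group is 90 percent". Alpha "is 0.05 (one side"), and beta "is 0.20. Calculated by PASS 11, the sample size in both groups is 157". After 10% dropout this becomes 175 per arm, and 180 per arm are recruited. No scale, response band or visit is attached to the rate, and the two arms' figures carry different names.
- **Primary criterion (5.2.1):** two response rates (obvious effective and effective), for both motor function and living ability, compared between and within groups. For fMRI there is a before-and-after comparison, which is not a rate.
- **Secondary outcomes:** the list in 5.1.2 omits the modified Barthel index, but the secondary criterion in 5.2.2 includes it twice: as a scale, and for a comparison of the same kinds of rate.
- **Timing (5.4):** primary measures are taken at the start and on days 14 and 28. Section 5.6 adds a telephone Barthel assessment four weeks after treatment.
- **Aim (2.1):** to assess the effect of the combined therapy "on limb dysfunction in patients with stroke in the convalescent stage".
- **Blinding (5.5):** none.

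**The concern.** A sample size calculation fixes the error rate and power of one particular test. Here a reader cannot tell which one. The rate could be the effective or the obvious effective band, on motor function or on living ability, at day 14 or day 28. Two bands on two domains already make four candidate between-group comparisons before the time point is considered, and the fMRI comparison is additional.

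Three outcomes share primary status, and Barthel appears in both tiers. The text therefore does not commit the trial to the result on which its conclusion will rest. The trial is open-label, so a fixed primary outcome is one of the few protections left against choosing the headline after the data are seen. Also at stake is whether the published 5% and 80% say anything about the claim the trial will eventually make.

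**Working it through.** **Inputs from section 2.3:** p1 = 0.80, p2 = 0.90, one-sided alpha 0.05, beta 0.20, dropout 10%, 180 recruited per arm. Allocation (2.5): "the case number of the experimental group and the control group is in a ratio of 1:1". **Assumed, because the article gives neither:** the decision rule across the three primaries, and the correlation between their test statistics (0 to 0.7).

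**1. Reproduce the plan's figure.** Two proportions, pooled variance, no continuity correction, mean rate 0.85:

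n = [z(1−α)·√(2·0.85·0.15) + z(1−β)·√(0.80·0.20 + 0.90·0.10)]² / 0.10²

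= [1.645·0.505 + 0.842·0.500]² / 0.01 = [0.831 + 0.421]² / 0.01 = 156.6, so **157 per arm**.

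Dropout: 157/0.90 = 174.4, so **175**. Both match section 2.3. With 180·0.90 = 162 evaluable per arm, power for this one comparison is 81.2%.

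**2. Any one of three suffices, each tested unadjusted at one-sided 5%.** Independent: 1 − 0.95³ = 14.3%. Correlated cases use an equicorrelated trivariate normal.

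**3. All three must succeed, each assumed to have 80% power.** Independent: 0.80³ = 51.2%. Correlated cases as before.

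| Assumed correlation | Family-wise error, any of three | Joint power, all three |
|---|---|---|
| 0 | 14.3% | 51% |
| 0.3 | 13.0% | 57% |
| 0.5 | 11.8% | 61% |
| 0.7 | 10.3% | 66% |

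Under the any-of-three rule, the chance of at least one success is not below the 80% of a single test (independent: 1 − 0.20³ = 99.2%). Under the all-three rule, the error stays at or below 5%.

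**4. A Bonferroni split (one-sided 0.05/3).** Error is held. Power for the 80% against 90% comparison falls to 65.4% at 162 per arm, and 224 evaluable per arm would be needed for 80%.

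**5. Sidedness, as separate information.** Replacing 1.645 by 1.960 gives [0.990 + 0.421]² / 0.01 = 198.96, so 199 per arm. Power at 162 per arm: Φ[(0.10·√162 − 0.990)/0.500] = Φ(0.566) = 71.4%.

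**6. What cannot be computed.** The article gives no effect size or standard deviation for the Barthel score, the Fugl–Meyer score or fMRI. Their actual power is unknown, and the 80% per test in step 3 is a premise only.

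**The case against.** **The rule for combining the primaries may be in an analysis plan that is not shown.** This stands. The article's silence on whether one or all must succeed is not itself the fault, and steps 2 to 4 illustrate possible rules; they do not describe this trial's conduct. Three parallel tests is itself a simplification of section 5.2.1.

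**A reader might infer that neither the 5% nor the 80% holds.** The documents do not support that. Under the any-of-three rule only the error fails; under the all-three rule or a Bonferroni split only the power fails. If one named rate is tested alone, or first in a fixed order, both figures hold for it.

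**A reader might also treat one-sided 5% as an error.** It is a declared choice, and the stated figures are consistent with it. It equals a two-sided 10% level, which is worth saying openly, but the 199 per arm and 71% belong to a different design.

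**Section 5.2.1 narrows the rate to motor function and living ability.** True, and it also gives fMRI its own criterion, so the lack of an fMRI response rate does not conflict with 2.3. But it leaves the scale and the band open.

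**Barthel in 5.2.2 may be only a drafting slip.** Quite possibly: the abstract and 5.1.1 make it primary, both secondary outcome lists omit it, and it is the follow-up scale in 5.6. The double listing alone gives little room for selection, but it is a contradiction in the current text and needs correcting.

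**Conclusion.** The point holds in this form: the stated one-sided 5% error and 80% power are arithmetically right for one 80% against 90% comparison, but the article does not identify that comparison, and the figures are not secured for a claim resting on three unranked primaries. The mismatch between 2.3, 5.1.1, 5.2.1 and 5.2.2 is in the text shown and does not depend on what an unseen analysis plan says.

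The size depends on the rule eventually applied: about 10–14% one-sided family-wise error in one case, or about 51–66% joint power in the other. Both ranges rest on assumed correlations of 0 to 0.7, and the second also on 80% power per test. They show how much is left open and are not estimates for this trial.

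**What to change.** 1. In 5.1.1, name one of the two clinical scales as the single primary outcome, with its response definition and time point. Fugl–Meyer fits the limb-dysfunction aim in 2.1. Barthel is also defensible: it is listed first, is used for eligibility, and daily living is part of the aim in section 7.
2. In 2.3, state that the 80% and 90% belong to that response rate, and give both arms' figures the same name. If the rates came from a different scale or definition, or if the primary becomes a mean score, the calculation has to be redone for the outcome chosen.
3. Test the other scale second, in a fixed sequence at the same level and only if the first succeeds. This keeps the family-wise error at 5% without splitting alpha.
4. Move fMRI to the mechanism outcomes, a heading that 5.2 already has.
5. Reconcile 5.2.2 with 5.1.1: delete Barthel there, or label it as the four-week follow-up measure only.
6. Optional and separate: state in 2.3 that one-sided 5% equals two-sided 10%, and that at two-sided 5% the same comparison has about 71% power with 162 evaluable per arm.

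The cost is wording in 2.3, the abstract, 5.1.1, 5.2.1 and 5.2.2, with the registry entry brought into line. The downside is that fMRI and the second scale lose equal primary status. No extra patients are needed as long as the 2.3 rates do belong to the outcome named.
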